## Methods

### Description of Participants

Participants aged between 18 and 75 years will be recruited through posters and flyers at strategic points and by word of mouth in order to support diversity. More specifically, we will recruit from the University of New Mexico’s hospital, clinics, and facilities (both from the Main and North campuses), and from the Albuquerque area in New Mexico. After showing interest, potential participants will be thoroughly informed about the study’s risks and benefits, and they will be asked to answer a medical and physical activity history questionnaire in order to assess eligibility [35]. The inclusion criteria will be presence of prediabetes (fasting glycemia between 100 and 125 mg/dL or glycated hemoglobin [HbA_1c_] between 5.7% and 6.4%) or T2D (fasting glycemia 126 mg/dL or above or HbA_1c_ 6.5% or above), diagnosed by a medical doctor. Glycemic status will be confirmed by assessing a fasting blood sample. Exclusion criteria will be renal failure; liver disease; uncontrolled hypertension (>160 mmHg systolic and/or >100 mmHg diastolic); history of severe cardiovascular problems; inability to perform resistance exercise; being pregnant or trying to become pregnant during the course of the study; use of oral contraceptives; and in case of being treated with biguanides (metformin), being on them for less than 3 months. If eligible, before initiating participation, subjects will sign the informed consent form previously approved by the Institutional Review Board (IRB). Participants will be reimbursed for expenses incurred due to the research and resulting from it. Participation will be discontinued in case of withdrawal of consent or in case of injury or sickness (eg, skeletomuscular injury and having a cold). We will report reasons for withdrawal and discuss the reasons qualitatively. Adverse events related or nonrelated to the research protocol experienced by participants during the study will be carefully recorded and reported in the final manuscript.

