### Study Type and Design

This study will be a crossover, 3-arm, randomized controlled trial. The protocol description followed the SPIRIT (Standard Protocol Items: Recommendations for Interventional Trial) [36] and the TiDieR (Template for Intervention Description and Replication) [37] guidelines (Figure 1 and Multimedia Appendices 1-4). Upon meeting eligibility criteria and agreeing to participate, participants will undergo an anthropometrics assessment, familiarization sessions, and strength assessment before randomly carrying out 3 separate experimental sessions (2 exercise and 1 control), with each session taking place over ~48 hours, over 3 consecutive days. The order of the sessions will be randomized and they will be separated by a minimum of 4 washout days.

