**Figure 1 figure1:**
[figure not shown]
SPIRIT (Standard Protocol Items: Recommendations for Interventional Trial) schedule of assessments at different time points. a: Sessions order is randomized with at least a 4-day washout period.

During experimental sessions, participants’ diets will be strictly controlled, and all food and drink will be provided to the participants. Glycemic control will be monitored using a CGM device throughout the experimental sessions. The exercise sessions will be matched for total volume load and session density, but proximity to concentric muscular failure (ie, incapacity to continue the set in the concentric phase of the movement) will be manipulated to vary the effort between the exercise sessions. The control session will follow identical procedures except that participants will remain sedentary for the same period of time they are to exercise in the exercise sessions.

Participants will be asked to refrain from moderate- to high-intensity physical exertion for 72 hours before the experimental sessions. The evening before the exercise or control sessions (day 1), at ~5 PM, participants will report to the laboratory to be instrumented with the CGM device and an accelerometer (to assess physical activity levels, refer to *Continuous Glucose Monitoring* subsection) and will receive dinner to be ingested at 6:30 PM and a snack to be ingested at 9:30 PM. The next morning (day 2), they will report fasted to the laboratory at 8:00 AM and ingest the provided breakfast at 8:30 AM. The exercise or control sessions will begin at 9:30 AM and will last ~50 minutes. They will perform 1 of 3 random sessions: a high-effort resistance exercise, a low-effort resistance exercise, or control session. After each session, psychological responses (perceived exertion, enjoyment, affect, discomfort, and self-efficacy) will be assessed.

After the session, participants will then be free to resume their daily activities after being given individualized meal bags and will be asked to consume lunch at 12:00 PM, a snack at 3:30 PM, dinner at 6:30 PM, and another snack at 9:30 PM, and in the following day (day 3), they will have breakfast at 8:30 AM, lunch at 12:00 PM, and a snack at 3:30 PM. After that, they will report to the laboratory between 5 and 6 PM to have the CGM device and accelerometer removed. Participants will be instructed to refrain from moderate- to high-intensity physical exertion until they are deinstrumented.

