Throughout the entire study period, participants will be explicitly instructed not to alter their prescribed medication and to report any prescription changes made by their medical doctor during participation. Any adverse events whether related or nonrelated to the research protocol experienced by participants during the study (eg, skeletomuscular injury and having a cold) will be carefully recorded and reported in the final manuscript. Figure 2 depicts the study design.

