### Statistical Analysis

The sample size was calculated using data from relevant literature using similar individuals and glucose-assessing tools (CGM) [11,14,52,53]. Conservative parameters were inserted in the G*Power program (Heinrich-Heine-Universität Düsseldorf, version 3.1.9.6) for a repeated measure ANOVA within interaction: effect size of 0.2 (for 24-hour average glucose concentrations), probability of error type **α** of 0.05, power (probability of error type 1 β) of 0.95, correlation among repeated measurements of 0.7 [54], and nonsphericity correction of 0.5 [55,56]. With these parameters, 15 individuals are required (actual power of 0.96). Considering a typical dropout rate of 25% to 40%, we will initially recruit 25 participants.

A collaborator outside the research team will double-enter data coded for allocation into a computer in separate spreadsheets, allowing the researcher responsible for data analysis to assess the data without access to allocation information. Allocation will only be revealed after statistical analyses are run. In case of doubts about data entry (missing values or values outside the reference range), the researcher responsible for data analysis will contact the collaborator outside the research team responsible for double entry of the data to check accuracy. There will be no interim analysis.

To ensure confidentiality, all study-related information will be securely stored at the study site. All participant information will be kept in locked file cabinets in areas with access controlled by the principal investigator. All laboratory specimens, reports, data collection, process, and administrative forms will be identified by a coded ID number only to maintain participant confidentiality. Records containing names or other personal identifiers, such as locator forms and informed consent forms, will be stored separately from study records identified by code number. No personal information from participants will be released outside the study. Full access to the complete dataset will be restricted to members of the research team.

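### The discontinuation rule ends participation for any sickness, even a cold, although the open-ended washout would let the session move, so a passing illness after randomisation becomes an avoidable incomplete crossover

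*Protocol article*

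**What the plan says.** **Discontinuation.** Protocol article, Description of Participants: participation ends when consent is withdrawn or "in case of injury or sickness (eg, skeletomuscular injury and having a cold". The sentence after it reads "We will report reasons for withdrawal and discuss the reasons qualitatively", so these cases are handled as withdrawals. No threshold of severity or duration is given, and no route back into the trial.

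**Spacing of sessions.** Study Type and Design: "The order of the sessions will be randomized and they will be separated by a minimum of 4 washout days". The Figure 1 legend agrees: "Sessions order is randomized with at least a 4-day washout period". No maximum interval is stated. The same section has the glucose monitor and accelerometer fitted on day 1 and removed on day 3 of each session, with food supplied for that session. Each session is therefore a separate unit.

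**Randomisation.** Under Randomization and Blinding, the envelope is opened after the fifth familiarization session.

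**Numbers and analysis.** Statistical Analysis requires 15 participants and continues: "Considering a typical dropout rate of 25% to 40%, we will initially recruit 25 participants". The analysis is to follow intention-to-treat, with a per-protocol analysis alongside. Under Results, data collection is expected to run from June 2024 to May 2025.

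**The concern.** The rule treats a temporary state at a visit (unwell this week) as the end of trial participation. By the time of randomisation a participant has completed five familiarization sessions and a 10-RM test. Under the rule as written, a cold after that point removes the person even if two of the three conditions have been recorded and the third could be held later.

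In a three-period crossover the loss is larger than one visit. The intention-to-treat statement keeps data from people who do not complete sessions as required, but it cannot supply a session that was never run. The Friedman test named in the plan needs all three conditions from each participant, as does a classical repeated-measures ANOVA. A participant with two of three sessions may therefore add little or nothing to the comparison. At stake are completeness and precision in a trial that needs only 15 completers and has little to spare if dropout is high.

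**Working it through.** **1. The plan's own recruitment figure.** Inputs from Statistical Analysis: 15 required, dropout 25% to 40%, 25 recruited. Formula: N / (1 − d).

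- d = 0.40: 15 / 0.60 = 25, an exact match.
- d = 0.25: 15 / 0.75 = 20.

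Treating each of 25 participants as completing independently:

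- d = 0.40: 25 × 0.60 = 15.0 expected completers; P(at least 15) = 0.59.
- d = 0.25: 25 × 0.75 = 18.75 expected completers; P(at least 15) = 0.97.

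At the upper dropout rate, then, 25 recruits leave no reserve. The 15 is taken as given here. It can be reproduced, but only with numbers of groups and measurements that the article does not state (for example 3 groups and 48 measurements, power 0.956).

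**2. Shortest possible timeline.** From the minimum intervals in Familiarization and Strength Tests and in Study Type and Design:

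| Step | Day |
|---|---|
| Familiarization 1 to 4, at least 48 h apart | 0, 2, 4, 6 |
| 10-RM test, at least 72 h later | 9 |
| Familiarization 5, at least 72 h later; envelope opened | 12 |
| Experimental session 1, after 72 h without exertion | 15–17 |
| 4 washout days, then session 2 | 22–24 |
| 4 washout days, then session 3 | 29–31 |

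The total is 31 days: 12 before randomisation and 31 − 12 = 19 after it. Only illness in the last 19 days can leave an incomplete crossover. Earlier illness is a loss before randomisation.

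**3. How many would be affected.** The document gives no illness rate. Assumption: 1 to 3 colds per adult per year, each leading to withdrawal, and all 25 randomised. Formula: P(at least one) = 1 − exp(−rate × days / 365).

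| Colds per year | 19 days after randomisation | Of 25 |
|---|---|---|
| 1 | 1 − exp(−0.052) = 0.05 | 1.3 |
| 2 | 1 − exp(−0.104) = 0.10 | 2.5 |
| 3 | 1 − exp(−0.156) = 0.14 | 3.6 |

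**4. What avoiding the loss could be worth.** The document does not say what part of the dropout allowance is illness, so a range is assumed. If 5, 10 or 15 of the 40 percentage points were avoidable illness withdrawals:

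| Dropout left | Recruits needed for 15 | Expected completers of 25 | P(at least 15) |
|---|---|---|---|
| 40% (as planned) | 25 | 15.0 | 0.59 |
| 35% | 24 | 16.25 | 0.77 |
| 30% | 22 | 17.5 | 0.90 |
| 25% | 20 | 18.75 | 0.97 |

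If illness withdrawals instead came on top of 40% dropout and took 5% to 15% of those remaining, expected completers would be 15 × 0.95 = 14.25 down to 15 × 0.85 = 12.75. The document does not settle which case applies.

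**The case against.** **The dropout allowance may already include illness.** The plan calls 25% to 40% typical, covers the upper end exactly and speaks of recruiting 25 initially, which does not rule out replacement. This stands, and it is why no loss of power can be claimed.

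**The article is condensed.** Rescheduling detail may sit in the full protocol, which is not shown. That excuses a missing rescheduling clause. It does not excuse a stated rule that ends participation.

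**Delay has a cost.** Loads come from a single 10-RM test and the low-effort repetitions from the fifth familiarization session. Strengths and Weaknesses says that a departure from that session's performance could introduce error, and it names menstrual phase as a possible confounder. A later date after an illness could widen both. This stands in part: that a session can be moved is an inference from the open-ended washout, and moving it is not free.

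**Stronger readings that the document does not support.**

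- A reader might infer that the protocol contradicts itself, because a cold is also among the adverse events: "eg, skeletomuscular injury and having a cold) will be carefully recorded and reported in the final manuscript". The Data Monitoring Committee section also has the board review respiratory symptoms. There is no contradiction. One event can be recorded, reviewed and also end participation.
- A reader might apply the same cold rates to all 31 days, get 8% to 23% (2 to 6 of 25) and conclude that the rule uses up much of the allowance of 10 losses. But 12 of those days precede randomisation, and the rate is an outside assumption.

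**Conclusion.** The point holds as a moderate weakness of design. As written, the rule turns a session that could be moved into a withdrawal, and after randomisation this leaves an incomplete three-period crossover. Nothing in the article makes that necessary, since it sets no upper limit on the interval between sessions.

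The likely size is 1 to 4 of 25 participants. It rests on the assumed cold rates, on the shortest timeline, on every cold leading to withdrawal and on all 25 being randomised. A longer actual schedule would raise the figure; fewer randomised, or a site that tolerates mild illness, would lower it. This is avoidable loss. It shows no error in the sample-size calculation or the planned analysis.

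**What to change.** Reconcile the discontinuation sentence in Description of Participants with the open-ended washout in Study Type and Design and with the intention-to-treat aim in Statistical Analysis. The text should let a temporary inability to attend move the outstanding session without ending participation, and should state that:

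- the randomised order, the minimum washout and the 72-hour limit on exertion are kept for the moved session;
- completed sessions are retained in the analysis;
- an illness that arises during a 48-hour recording is flagged for the per-protocol analysis.

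Which illnesses or injuries preclude exercise is a clinical matter for the investigators, and no rule is proposed here.

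The cost is a reworded rule and no extra participants. A few people stay in the trial longer, and a delayed session may drift somewhat from the 10-RM loads and fifth-session repetitions. Reporting the actual interval between sessions would let readers judge that drift.

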### Study Type and Design

This study will be a crossover, 3-arm, randomized controlled trial. The protocol description followed the SPIRIT (Standard Protocol Items: Recommendations for Interventional Trial) [36] and the TiDieR (Template for Intervention Description and Replication) [37] guidelines (Figure 1 and Multimedia Appendices 1-4). Upon meeting eligibility criteria and agreeing to participate, participants will undergo an anthropometrics assessment, familiarization sessions, and strength assessment before randomly carrying out 3 separate experimental sessions (2 exercise and 1 control), with each session taking place over ~48 hours, over 3 consecutive days. The order of the sessions will be randomized and they will be separated by a minimum of 4 washout days.

**Figure 1 figure1:**
[figure not shown]
SPIRIT (Standard Protocol Items: Recommendations for Interventional Trial) schedule of assessments at different time points. a: Sessions order is randomized with at least a 4-day washout period.

During experimental sessions, participants’ diets will be strictly controlled, and all food and drink will be provided to the participants. Glycemic control will be monitored using a CGM device throughout the experimental sessions. The exercise sessions will be matched for total volume load and session density, but proximity to concentric muscular failure (ie, incapacity to continue the set in the concentric phase of the movement) will be manipulated to vary the effort between the exercise sessions. The control session will follow identical procedures except that participants will remain sedentary for the same period of time they are to exercise in the exercise sessions.

Participants will be asked to refrain from moderate- to high-intensity physical exertion for 72 hours before the experimental sessions. The evening before the exercise or control sessions (day 1), at ~5 PM, participants will report to the laboratory to be instrumented with the CGM device and an accelerometer (to assess physical activity levels, refer to *Continuous Glucose Monitoring* subsection) and will receive dinner to be ingested at 6:30 PM and a snack to be ingested at 9:30 PM. The next morning (day 2), they will report fasted to the laboratory at 8:00 AM and ingest the provided breakfast at 8:30 AM. The exercise or control sessions will begin at 9:30 AM and will last ~50 minutes. They will perform 1 of 3 random sessions: a high-effort resistance exercise, a low-effort resistance exercise, or control session. After each session, psychological responses (perceived exertion, enjoyment, affect, discomfort, and self-efficacy) will be assessed.

After the session, participants will then be free to resume their daily activities after being given individualized meal bags and will be asked to consume lunch at 12:00 PM, a snack at 3:30 PM, dinner at 6:30 PM, and another snack at 9:30 PM, and in the following day (day 3), they will have breakfast at 8:30 AM, lunch at 12:00 PM, and a snack at 3:30 PM. After that, they will report to the laboratory between 5 and 6 PM to have the CGM device and accelerometer removed. Participants will be instructed to refrain from moderate- to high-intensity physical exertion until they are deinstrumented.

Throughout the entire study period, participants will be explicitly instructed not to alter their prescribed medication and to report any prescription changes made by their medical doctor during participation. Any adverse events whether related or nonrelated to the research protocol experienced by participants during the study (eg, skeletomuscular injury and having a cold) will be carefully recorded and reported in the final manuscript. Figure 2 depicts the study design.

**Figure 2 figure2:**
[figure not shown]
Study design. CGM: continuous glucose monitoring.

### Anthropometrics

Body weight and height will be measured on an analog scale and a stadiometer, respectively, and BMI (kg/m^2^) will be calculated. Subsequently, the waist circumference will be measured with a measuring tape parallel to the ground over the umbilicus. Body composition will be evaluated using multifrequency bioelectrical impedance analysis (Bioelectrical impedance analysis, InBody 770) following manufacturer instructions.

### Familiarization and Strength Tests

Familiarization and strength tests will be performed as previously described [24-26]. Briefly, familiarization will consist of 5 sessions separated by at least 48 hours. In each session, participants will perform 3 sets of 8-10 repetitions of 7 exercises that target major muscle groups (hex bar squat, seated chest press, leg press, lat pulldown, leg extension, shoulder press, and leg curl; Figure 3), and load will be gradually increased throughout the familiarization sessions so that by the fifth session, participants will be able to perform the exercises with a high degree of effort (9-10 out of 10) based on the OMNI-Resistance Exercise scale [38]. Participants will also be familiarized with the psychological assessments during the familiarization period.

**Figure 3 figure3:**
[figure not shown]
Exercises that will be prescribed for the strength exercise sessions: (1) hex bar squat, (2) seated chest press, (3) leg press, (4) lat pulldown, (5) leg extension, (6) shoulder press, and (7) leg curl.

At least 72 hours after the fourth familiarization session, participants will perform the 10–repetition maximum (RM) tests [39,40] (the highest load one can lift for 10 complete repetitions with proper form) in each of the 7 exercises. After an initial 5-minute warm-up walking on a treadmill (~3-4 km/h, very light intensity) and 1 set with low load (12 repetitions, ~40%-50% 1RM, ~3-4 on the OMNI scale), the weight in each exercise will be adjusted to the weight used in the last familiarization session plus 5% to 10%, and participants will be instructed to attempt to perform 11 repetitions with good form (ie, with a full range of motion and tempo ~2:1 sec). If they perform the 11 repetitions with good form, the weight will be increased by 5% to 10%, and they will be given 180 seconds to recover and will make another attempt. Load will be increased until they can perform 10 repetitions or fewer with good form. If they perform fewer than 10 repetitions, the Brzycki equation [41,42] will be used to estimate participant’s 10-RM. All tests will be performed under the supervision of the same research team member and the load corresponding to the 10-RM in each of the exercises will be used in the exercise sessions (described in *Exercise and Control Sessions* subsection).

At least 72 hours after the strength assessments, participants will perform a fifth and final familiarization session. This familiarization session will be equal to the high-effort session (described below). Participants will perform the 7 exercises, 3 sets per exercise (total of 21 sets), aiming at 8 repetitions per set, using the load corresponding to their 10-RM. Participants will be asked to rate their exertion after each set using the OMNI scale, to ensure they are performing the sets with high effort (>8 on the OMNI scale). The resting period between exercises and sets will be 120 seconds. The main outcome from the fifth familiarization session is the number of repetitions the participant can perform in each set of the 7 exercises.

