## Introduction

Type 2 diabetes (T2D) is a disease in which peripheral insulin resistance associated with pancreatic beta-cell dysfunction leads to chronically elevated blood glucose levels [1]. If left unchecked over long periods of time, high glucose levels lead to vascular complications such as increased risk of cardiovascular diseases, diabetic nephropathy, neuropathy, retinopathy, and lower limb amputation [2]. In 2021, a total of 0.7 million people died due to diabetes or its complications in the United States [2], placing diabetes-related deaths as the eighth leading cause of death. T2D is preceded by prediabetes, a condition where blood glucose levels are higher than normal, but not high enough to be considered T2D [3]. The risk of individuals living with prediabetics developing T2D at some point in their life is around 50% [4], and approximately 1 in 3 Americans aged 18 years or older are currently living with prediabetes. The number of people living with diabetes in the United States was 32.2 million in 2021, and it is expected to increase to 36.3 million in 2045 [2]. Diabetes represents a great economic burden to society, as diabetes-related costs in the United States in 2021 were US$ 379.5 billion [2]. Approximately 95% of all diabetes cases are T2D [5].

It is an indisputable fact that exercise is a cornerstone for the prevention and treatment of prediabetes and T2D [6,7]. Of note, even an acute bout of exercise has profound positive effects on glucose metabolism [8]. In fact, exercise training effects on improved insulin sensitivity may be lost in as little as 6 days after the last exercise session in individuals living with T2D [9,10], suggesting the positive effects of exercise on glycemic control can be largely attributed to the acute improvements observed in the hours or days after each exercise bout [11]. Thus, understanding the acute effects of exercise on glucose metabolism is important to optimize exercise prescription for the prevention and treatment of T2D. Although aerobic exercise is usually the default choice for T2D treatment and prevention [7], resistance exercise is also a viable option for physically inactive individuals living with prediabetes and T2D [12,13].

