### Randomization and Blinding

After the fifth familiarization session, random allocation of the order of the experimental sessions’ participants will carry out will be performed as previously described [24-26]. The order in which the experimental sessions will be held will be randomized with the aid of the website. A collaborator not directly involved in any phase of the research (conceptualization, data collection and analysis, and reporting) will print the random orders generated by the program, insert them inside opaque, sequentially numbered envelopes, and seal them. After completing the fifth familiarization day, the envelope will be opened, and the sequence of experimental sessions will be revealed.

Due to characteristics inherent to this trial (resistance exercise), blinding of participants and researchers to exercise or control situations is not possible. However, participants and researchers will be blinded to CGM results (the blind model will be used). Furthermore, data and statistical analysis will be performed by a statistician blinded to groups and participants’ identities, as previously described [24-26].

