### Diet and Physical Activity Levels

During the ~48-hour experimental situations, diet prescription will follow American Diabetes Association recommendations [49,50] to ensure a personalized diet based on their estimated energy requirements. Meals and snacks will be provided in individualized, pre-weighted packages and will be composed of ~55% carbohydrate, ~15% protein, and ~30% fat. The timing of ingestion will be strictly controlled to ensure a standardized diet. Diet prescription will be done by a registered dietitian nutritionist. The diet will be designed to meet the energy requirements as calculated with the Cunningham equation [51] multiplied by a physical activity level of 1.2 [11].

Participants will be instructed to maintain their habitual physical activity levels, and to not perform moderate- to high-intensity physical activity 72 hours before and during the experimental sessions. Physical activity levels will be assessed using a commercially available accelerometer (GT3X, ActiGraph).

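### The 4-day washout is not applied before period 1, so a full high-effort bout may precede first-period glucose monitoring by 72 h, against at least 127.5 h in later periods

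*Protocol article*

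**What the plan says.** All references are to the protocol article.

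- **Washout (Study Type and Design).** "The order of the sessions will be randomized and they will be separated by a minimum of 4 washout days". "They" are the three experimental sessions; the Figure 1 note ties the same 4-day period to the randomized sessions.
- **Definition of a session (same section).** Each experimental session is the whole monitoring episode: "with each session taking place over ~48 hours, over 3 consecutive days".
- **Exertion rule (Study Type and Design).** "Participants will be asked to refrain from moderate- to high-intensity physical exertion for 72 hours before the experimental sessions". Diet and Physical Activity Levels repeats it: participants are "to not perform moderate- to high-intensity physical activity 72 hours before and during the experimental sessions".
- **Familiarization (Familiarization and Strength Tests).** "familiarization will consist of 5 sessions separated by at least 48 hours", with at least 72 h from the fourth session to the 10-RM tests and at least 72 h from those tests to the fifth session. Of the fifth session it says: "This familiarization session will be equal to the high-effort session (described below". That is 21 sets at the 10-RM load, with ratings above 8 on the OMNI scale.
- **Next step (Randomization and Blinding).** "After completing the fifth familiarization day, the envelope will be opened, and the sequence of experimental sessions will be revealed". No interval to period 1 is given here.
- **Persistence of effect (Introduction).** The acute effect of a resistance bout is said to last at least 24 hours. Separately, "exercise training effects on improved insulin sensitivity may be lost in as little as 6 days after the last exercise session".
- **Analysis (Statistical Analysis).** The ANOVA has experimental condition as its only factor.

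**The concern.** In a crossover, each period should start from a comparable state. The protocol protects periods 2 and 3 with a washout, but it places an identical bout just before period 1 and does not apply the washout to it. The spacing of every earlier familiarization and testing step is stated; this one is not. Period 1 also follows a block of six resistance visits.

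If any effect of that bout or block remains when the sensor goes on, first-period glucose is shifted for whichever condition comes first. A participant who has control first would supply a reference that is not fully rested, and the protocol measures the exercise effect as change from control. A participant who has an exercise session first would show that session plus the residue. With 15 participants and no period term, an uneven spread of conditions over period 1 would pass such a shift into the contrasts.

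**Working it through.** **Inputs (Study Type and Design).** CGM starts on day 1 at about 5 PM. The exercise or control bout starts on day 2 at 9:30 AM, 16.5 h later. CGM is removed on day 3 between 5 and 6 PM; 5 PM is used here. The washout is at least 4 days and the exertion rule is 72 h. These gaps are design minimums, so the plan has no calculated figure to reproduce.

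**1. Gap before periods 2 and 3, from an exercise bout to the next CGM start.**
- Day 2, 9:30 AM to day 3, 5 PM = 31.5 h.
- Four days counted as 96 h from removal: 31.5 + 96 = 127.5 h.
- Four full calendar days (days 4 to 7), with CGM start at 5 PM on day 8: 31.5 + 120 = 151.5 h.
- If the preceding period was control, the last bout lies further back, so these are floors.

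**2. Gap before period 1, from the fifth familiarization session to CGM start.**
- The session is defined as the whole ~48 h, so the 72 h run to its start: 72 h to CGM start and 72 + 16.5 = 88.5 h to the bout.

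**3. Comparison.**
- 72 / 127.5 = 56%; 72 / 151.5 = 48%.
- Shortfall: 127.5 − 72 = 55.5 h (2.3 days), or 151.5 − 72 = 79.5 h (3.3 days).

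**4. Length of the preceding block at minimum spacing.**
- Three gaps of 48 h and two of 72 h: 144 + 144 = 288 h, or 12 days, for six resistance visits.

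**5. Effect of a period-1 shift d on a contrast between two conditions.** Each participant contributes to both conditions, so the error in the contrast is d × (share of participants with A first − share with B first).
- *Simple randomization, N = 15 (assumption).* The expected difference in shares is 0, and its SD is √[(2/3)/15] = 0.21. The error has mean 0 and SD 0.21d. The simulated 95% range of the difference is −0.4 to 0.4. Two given conditions differ by 3 or more in first-period count with probability 0.43.
- *The six orders in blocks of six (alternative assumption).* Two complete blocks are balanced, and the last 3 participants are drawn without replacement from 6 orders, 2 starting with each condition. The variance of the difference in counts is 3 × (2/3) × (3/5) = 1.2, so the SD is √1.2 / 15 = 0.07. The counts differ by at most 2.

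**6. Does the stated model remove it?** No. With condition as the only factor, a shift common to period 1 stays in the error and in any chance imbalance. With 15 complete participants, a repeated-measures ANOVA has (15 − 1)(3 − 1) = 28 residual degrees of freedom; a three-level period factor uses 2 and leaves 26.

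**The case against.** The strongest reply is that period 1 is not unprotected. The 72-hour rule covers all experimental sessions, including the first, and a high-effort bout plainly falls under it. The document gives an acute effect of at least 24 hours and nowhere says that one remains at 72 h. No value for d is available, so the size of the error in glucose units is unknown and may be trivial. The 0.21 depends on simple randomization, and the protocol says only that a website generates the orders. Familiarization is described briefly with reference to earlier reports, and the schedule and design figures are not visible here; either might show the interval.

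Most of this stands and limits the point. It does not remove it: the text gives a washout rule, applies it after two identical bouts and not after the third, and no stated rule closes the gap.

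Three stronger readings are tempting, and the document does not support them.
- *Period 1 may start less than 72 h after the bout.* If the 72 h ran only to the 9:30 AM bout, CGM could start at 72 − 16.5 = 55.5 h. But the protocol defines an experimental session as the whole ~48-hour episode, so 72 h is the floor to CGM start.
- *The 6-day figure shows carryover.* That statement concerns loss of training effects and says they may go in as little as 6 days; it does not say that one bout acts for 6 days. The trial's own 127.5 h is also below 144 h, so 6 days is not a standard that the later periods clearly meet.
- *The control condition is biased and the exercise effect shrunk.* Control placed first pulls the contrast one way and exercise placed first pulls it the other. Under random order these cancel in expectation.

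**Conclusion.** The asymmetry is established from the text: a high-effort bout may precede CGM start by 72 h in period 1, against a minimum of 127.5 h (or 151.5 h) in periods 2 and 3. That this shifts period-1 glucose is possible and not shown.

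If there is a shift d, it adds noise and chance imbalance, with no expected bias towards any condition. The added error per contrast has SD about 0.21d under simple randomization of 15 participants and about 0.07d with orders in blocks of six; both allocation schemes are assumptions. No sample-size, power or alpha figure changes. The point is a cheap improvement that puts period 1 on the same footing as the others; it does not threaten the trial's validity.

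**What to change.** - **Schedule.** Reconcile the familiarization and washout passages. State a minimum time from the fifth familiarization session to period-1 CGM start that is at least what the trial's own washout gives between an exercise bout and the next CGM start, about 127.5 h. Count it from the last resistance bout. Extending the 4-day rule to run from the familiarization session would give only about 96 h and leave the periods unequal. The same edit should say whether 4 washout days means 96 h from device removal or four full calendar days; under the second reading the matching figure is 151.5 h.
- **Analysis.** Include period as a factor alongside condition in the crossover model, so that a shift common to period 1 is taken out of the condition contrasts.

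**Cost.** About 2.3 extra days before period 1 (3.3 under the calendar-day reading) for participants who would otherwise be booked at the 72-hour minimum, and 2 of 28 residual degrees of freedom. No extra visits or staff.
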